**d. What are the specific stopping rules for the research?**

Interim Analysis and Criteria For Halting The Study

During the course of the trial we have monitored for adverse events potentially related to the immunosuppressive agents used in each of the four arms of the study. Interim analyses performed after enrollment of 60 and 140 patients have shown not only generally low and acceptable rates of study-drug related adverse events, but that specifically the rates of adverse events are statistically identical between the study arms.

The originally approved stopping rules for this study have become effectively obsolete, as the study has matured beyond the point where there is any possibility that additional adverse events could exceed the number prescribed as tolerable under the stopping rules algorithm.

While we consider that the safety of the immunosuppressive agents being used in this trial has been well demonstrated, we will continue the policy of stopping enrollment in the study, pending a complete investigation by the Principal, Co-principal, and Secondary investigators, if either of the following should occur:

1. Death of one subject due to an adverse drug reaction
2. A probability of life life-threatening, adverse drug reactions, including pulmonary edema requiring intubation, myocardial infarction, or hypotension requiring significant drug treatment.

Conditions that may warrant termination of the study include, but are not limited to:

- The discovery of an unexpected, serious, or unacceptable risk to patients enrolled in the study.
- The decision on the part of the Investigator to suspend or discontinue testing, evaluation, or development of the clinical program.
- Insufficient adherence to protocol requirements.

Study termination and follow-up will be performed in compliance with the conditions set forth in 21 Code of Federal Regulations (CFR) 312.

**e. Is there a DSMB for this research study?** No.

-If **no**, describe the process of ongoing data analysis:

**1) What is the frequency of data analysis?**

A formal interim analysis of the accumulated study data was conducted after accrual of 60 subjects and again at 140 subjects. The findings of the second 140 subject interim analysis were peer-reviewed and published in the journal *Transplantation*. Outcome data are continually being collected and audited as subjects progress through the initial subsequent phases of the study. An additional formal analysis of the induction phase will be performed at the accrual of the final study subjects. The optimal timing of a formal analysis of the outcome of the calcineurin inhibitor withdrawal phase will be defined as further experience of calcineurin inhibitor withdrawal accumulates.

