**b. What is the statistical or other justification for the maximum accrual requested?**

A detailed analysis of the statistical power and sample size requirements of this study was prepared by [name] in July 2005, and is attached to this 5-year re-write in fulfillment of the requirements of this section. This statistical power and sample size analysis concludes that the study goals can be met with a total enrollment of 200 subjects, which is sufficient to compensate for a 10% drop-out rate. Our experience with this study to date appears to substantiate this enrollment size as being appropriate to meet study goals.

**c. For multicenter protocols, what is the total number of subjects to be enrolled at all sites?** NA – this is a single-center protocol.

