**METHODS AND PROCEDURES (10-12)**

**10. Methods and Procedures Applied to Human Subjects**

a. Briefly describe the study design (e.g. randomized, double blind, cross-over, phase III).

This is a prospective, randomized, non-blinded 2 x 2 factorial comparison of clinical outcomes in 180 renal transplant recipients receiving either a single dose of rATG at 6 mg/kg or 4 doses given every other day at 1.5 mg/kg/dose. Immediately after renal transplantation, each of these groups will undergo our clinically-standard early steroid withdrawal; approximately 6 months later, half the subjects in each group will be switched to maintenance immunosuppression using Sirolimus/MMF.

**b. Are there any tests performed prior to signing of the consent form in order to determine eligibility for this research protocol?** No.

**c. Describe sequentially all procedures, interventions and evaluations to be applied to subjects, and identify any that are experimental or performed exclusively for research purposes.**

Participants must sign a written consent form prior to initiation of any study procedure.

At the time of transplantation, the participant will be randomized to one of 4 groups: (1) single-dose rATG at 6 mg/kg plus rapamycin and tacrolimus maintenance immunosuppression, (2) divided-dose (4 doses) rATG given every other day at 1.5 mg/kg/dose plus rapamycin and tacrolimus maintenance, (3) single-dose rATG plus rapamycin and tacrolimus maintenance with conversion after 6 months to rapamycin and mycophenolate mofetil maintenance, and (4) divided-dose rATG plus rapamycin and tacrolimus maintenance with conversion after 6 months to rapamycin and mycophenolate mofetil maintenance. Given the long-term effects of rATG, single-dose versus divided-dose administration may have a differential impact on the patient’s requirements for maintenance immunosuppression (see section II.2). For this reason, we are randomizing patients to the 4 treatment groups delineated above.

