1. Cumulative calcineurin nephrotoxicity/ transplant nephropathy per clinically-indicated and protocol surveillance biopsies (Banff grading criteria)
2. Renal function by either measured 24-hour urine creatinine clearance at 1, 3, 6, 12 and 24 months or calculated GFR (Glomerular Filtration Rate) by using the abbreviated MDRD (aMDRD) formula and patient serum creatinine and demographic data. This may be calculated from routine blood draws, allowing multiple data points to be collected within each month.

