**19*.*** **Risk-Benefit Relationship**

**a. What is the relative risk-benefit relationship of the research?**

The primary benefit to patients receiving the single dose of rATG may be an increase in tolerance of the graft. If this occurs, these patients may require reduced levels of maintenance immunosuppression. This would translate into less exposure to potentially toxic side effects and reduced cost.

Further, if patients are able to tolerate conversion to maintenance immunosuppression with sirolimus and low-dose mycophenolate mofetil, this, too would lower exposure to potentially toxic side effects and further reduce cost and inconvenience since management of both tacrolimus and sirolimus require routine blood samples for trough levels. The added risk of another immunosuppressive agent is acceptable since all of these patients require immunosuppression to prevent loss of their graft. Adding low-dose mycophenolate mofetil should provide added protection against the risk of rejection when tacrolimus is discontinued.

**b. What is the relative risk-benefit relationship of the research compared with the risk-benefit relationship of any alternatives?**

Our group recently published an interim analysis of the first 142 patients where we presented evidence that single-dose administration of rATG is safe and associated with improved early renal function when compared to conventional alternate day dosing. Our analysis was unable to detect any differences between groups in relation to rATG-related adverse events, patient and graft survival, acute rejection, or chronic allograft nephropathy rate at six months. However, we did se clear evidence for significantly improved graft function in the group receiving the single rATG dose. A copy of the peer-reviewed published manuscript detailing these findings has been included for the board’s review. It is our belief that this dosing regimen offers the subject a favorable risk-benefit relationship when compared to conventional divided-dose administration.

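### Item 15e(1) ties the final induction analysis to last accrual rather than completed follow-up, and leaves the date of the withdrawal analysis open in a non-blinded trial

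*Protocol*

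**What the plan says.** Three statements in Protocol item 15e(1) matter here.

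- Past looks: "A formal interim analysis of the accumulated study data was conducted after accrual of 60 subjects and again at 140 subjects".
- Next look: "An additional formal analysis of the induction phase will be performed at the accrual of the final study subjects".
- Withdrawal phase: the timing of its formal analysis "will be defined as further experience of calcineurin inhibitor withdrawal accumulates".

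Other parts of the protocol give the context.

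- Item 1 lists two primary goals: the single- versus divided-dose comparison, and the conversion away from tacrolimus at about month 6.
- Item 10c makes biopsy-graded nephrotoxicity or nephropathy the first primary endpoint, with surveillance biopsies at 6, 12 and 24 months. The second is "Renal function by either measured 24-hour urine creatinine clearance at 1, 3, 6, 12 and 24 months or calculated GFR".
- Item 10a describes the design: "This is a prospective, randomized, non-blinded 2 x 2 factorial comparison of clinical outcomes in 180 renal transplant recipients". Item 15e says there is no DSMB. Item 15e(2) gives further analyses to the group that did the second look, which is programme staff with a contract statistician.
- Item 19b reports that the published interim analysis, there of 142 patients, found "significantly improved graft function in the group receiving the single rATG dose".

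**The concern.** A final analysis should be timed by when the endpoint is known, not by when the last subject enters. Randomisation takes place at transplantation, so on the day of last accrual the newest subjects have no outcome. The final look exists to add these later subjects to what is already published, and their data would be the least complete.

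For primary goal 2 the problem is discretion. The people who choose the analysis date know the treatment assignments and handle the outcome data continually. A date not fixed in advance can be moved, knowingly or not, towards a favourable moment, and nobody could later show that it was not.

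A third matter follows from the second look. A significant result on a primary endpoint is already in print, and a further formal test of the same question is planned. The protocol does not say which of the two carries the confirmatory claim.

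**Working it through.** **Trigger against endpoint schedule.** These follow from items 10c and 15e(1).

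| Outcome | Earliest scheduled value | Available at last accrual? |
|---|---|---|
| Calculated GFR | first days after transplant | not for the last subject |
| Creatinine clearance | month 1 | not for subjects accrued in the preceding month |
| Surveillance biopsy | month 6 | not for subjects accrued in the preceding 6 months |

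The protocol gives no accrual rate, so the number affected cannot be computed. The gap falls on the newest recruits, and only 180 − 140 = 40 to 200 − 140 = 60 subjects are new since the second look.

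**The trigger is itself ambiguous.** Items 3a and 10a give 180 subjects. Item 3b says "study goals can be met with a total enrollment of 200 subjects, which is sufficient to compensate for a 10% drop-out rate". The two figures are linked by 180 / (1 − 0.10) = 200, but the protocol does not say which one ends accrual. Both are carried below.

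**Withdrawal analysis.** There is no date to check. The last scheduled study visit and protocol biopsy fall at month 24; years 3 to 5 are covered by record review (item 10c). Month 24 is therefore a natural fixed point already in the schedule.

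**Size of the multiplicity question.** The protocol states no significance level or error rate, so there is no figure to reproduce.

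Assumptions: two-sided 5% at each look (|z| > 1.96), and information proportional to subjects accrued.

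Formula: corr(Z_i, Z_j) = √(n_i / n_j) for n_i < n_j; overall error = 1 − P(|Z_k| < 1.96 at every look), by multivariate normal integration.

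Correlations: √(140/180) = 0.882; √(140/200) = 0.837; √(60/140) = 0.655; √(60/180) = 0.577; √(60/200) = 0.548.

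| Efficacy looks | Overall error | Constant nominal p that holds 5% |
|---|---|---|
| 140, 180 | 7.2% | 0.034 |
| 140, 200 | 7.6% | 0.032 |
| 60, 140, 180 | 10.5% | 0.0226 |
| 60, 140, 200 | 10.8% | 0.0218 |

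A simulation of one million runs gave 10.5% and 10.8% for the two three-look rows. Using 142 in place of 140 (with 60 and 180) leaves 10.5%. An O'Brien-Fleming-type rule over three looks would put the final nominal p at about 0.043 (N = 180) or 0.045 (N = 200).

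These are probabilities that at least one look is significant under no effect. If only the final test can support the claim, and no look can stop the trial for efficacy, the error of that test stays at 5%.

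**The case against.** **Timing.** The accrual phrase sits in an answer about how often data are analysed, and may loosely mean once enrolment is complete. The look at about 140 subjects did report six-month nephropathy (item 19b), so a look labelled by accrual has included follow-up outcomes. The mixed model in item 10e can also use partial GFR series. Part of this stands: the text does not prove that the last subjects will be analysed without outcomes. But it names accrual as the trigger and gives no follow-up cut-off, and a mixed model for GFR does nothing for a missing biopsy.

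**Withdrawal date.** A reader might infer that by-arm results will choose the date. The protocol does not say so; experience may mean only the number converted and their time on the regimen. What stands is that nothing in the text excludes the other course.

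**Multiplicity.** A reader might infer that the trial runs three efficacy tests with no error control, at a false-positive rate of 10.5%, and so needs p < 0.0226 at the end. The documents do not support this.

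- No significance level is stated for any look. The 2005 power analysis and any SAP are not at hand and may contain an adjustment.
- An efficacy result is documented only for the look at about 140. For the look at 60, item 15d reports adverse events, although item 15e(1) speaks more broadly of study data.
- Item 15d has no rule for stopping on efficacy, and accrual continued after the positive look.
- Item 19b already calls the published result interim, and item 11b(2) describes the study as a possible pilot for a larger trial.
- The threshold depends on the number of efficacy looks, the final N and the boundary type. The working gives values from 0.0218 to 0.045.

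**Conclusion.** Two parts hold on the text alone. The final induction analysis is tied to accrual although the primary endpoints need follow-up, and the analysis date for primary goal 2 is deliberately left open in a non-blinded trial analysed by its own team without a DSMB. Both should be fixed. Neither shows that bias has occurred.

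The multiplicity part holds only conditionally. If the published interim result and the final result may both count as success, overall error is about 7.2% to 7.6% with two efficacy looks, or 10.5% to 10.8% with three, assuming unadjusted two-sided 5% at each look and a final N of 180 to 200. If the final analysis alone is confirmatory, no adjustment is needed. The protocol should say which applies. It does not dictate any single threshold.

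**What to change.** Amend item 15e(1) before the final look.

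1. Run the final induction analysis once, when the last randomised subject has completed month 6, including the month-6 biopsy where one is done. State whether final accrual means 180 or 200.
2. Fix the withdrawal analysis now at the last randomised subject's month-24 visit. State that no earlier by-arm efficacy tabulation of post-month-6 data will be used to set the date. Safety monitoring is unaffected.
3. Name the final induction analysis as the sole confirmatory test of that comparison, and label the result at 140/142 subjects as interim wherever it is cited. Alternatively, if the interim result is also to count as a success, state how many efficacy looks were made and give an adjusted threshold for them.

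The cost is three sentences and an induction report about six months later. No extra subjects, visits or procedures are needed.

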**2) Who will perform the analysis?**

The initial interim analysis of the first 60 subjects was performed by [name] of the UNMC College of Public Health Department of Biostatistics. The second interim analysis of the 140 subjects was performed jointly by staff of the Kidney/Pancreas Transplant Program ([name], [name], and [name]) and [name] of Sigma Analytics. Ongoing analyses of further study data will be performed by this same group.

**16. Potential Benefits to the Subject**

**What are the potential benefits to the subject associated with the research?**

If the participant is randomized to the group which receives the single-dose of rATG, and this dose proves to promote tolerance of a transplanted kidney, then the participant may experience this benefit.

If the participant is randomized for conversion to sirolimus and low-dose mycophenolate mofetil maintenance immunosuppression beginning at 6 months, and this proves to be effective in preventing rejection of the transplanted kidney, they may benefit from decreased cost of medicines, and lower exposure to potentially serious side-effects of tacrolimus.

Having a kidney biopsy at 24 months will provide the subject’s physicians with additional information about the transplanted kidney. If kidney rejection is detected, then this biopsy may allow the physicians to begin anti-rejection treatment earlier. In addition, if biopsy results show moderate to severe chronic allograft nephropathy, the physicians would be able to adjust the immunosuppression therapy to minimize progression of the nephropathy.

The participant may experience no direct benefit.

**17. Potential Benefits to Society**

**What are the potential benefits to society that may result from this research?**

This study may help future patients who undergo kidney transplantation.

**18.** **Alternatives to Participation**

**a. What are the alternatives available to the subject in the *non-research* context which may be of reasonable benefit to the subject?**

**Standard clinical practice at UNMC for kidney transplant recipients is rATG given in four doses every other day starting on the day of transplant. Patients who do not wish to participate in this protocol would still receive the standard rATG dosing.** Standard maintenance anti-rejection treatment following kidney transplant is tacrolimus or cyclosporine with or without one or more of the following: corticosteroids (prednisone, prednisolone), mycophenolate mofetil and/or sirolimus.

**b. Would any of the interventions in the study be available to the subject if they did not elect to participate in the study?**

No, rATG induction given as a single-dose is available only in the context of this research study. Subjects who chose not to participate would receive standard of care immunosuppression induction, which currently is four doses of rATG given every other day beginning the day of transplant.

**19*.*** **Risk-Benefit Relationship**

**a. What is the relative risk-benefit relationship of the research?**

The primary benefit to patients receiving the single dose of rATG may be an increase in tolerance of the graft. If this occurs, these patients may require reduced levels of maintenance immunosuppression. This would translate into less exposure to potentially toxic side effects and reduced cost.

Further, if patients are able to tolerate conversion to maintenance immunosuppression with sirolimus and low-dose mycophenolate mofetil, this, too would lower exposure to potentially toxic side effects and further reduce cost and inconvenience since management of both tacrolimus and sirolimus require routine blood samples for trough levels. The added risk of another immunosuppressive agent is acceptable since all of these patients require immunosuppression to prevent loss of their graft. Adding low-dose mycophenolate mofetil should provide added protection against the risk of rejection when tacrolimus is discontinued.

**b. What is the relative risk-benefit relationship of the research compared with the risk-benefit relationship of any alternatives?**

Our group recently published an interim analysis of the first 142 patients where we presented evidence that single-dose administration of rATG is safe and associated with improved early renal function when compared to conventional alternate day dosing. Our analysis was unable to detect any differences between groups in relation to rATG-related adverse events, patient and graft survival, acute rejection, or chronic allograft nephropathy rate at six months. However, we did se clear evidence for significantly improved graft function in the group receiving the single rATG dose. A copy of the peer-reviewed published manuscript detailing these findings has been included for the board’s review. It is our belief that this dosing regimen offers the subject a favorable risk-benefit relationship when compared to conventional divided-dose administration.

**FINANCIAL OBLIGATIONS AND COMPENSATION (20-21)**

**20. Financial Obligations of the Subject**

**a. What financial obligations will the subject incur as a result of participating in the study?**

The subject (or subject’s third party payer) will be responsible for all standard costs incurred by receiving a kidney transplant. This includes the cost of the rATG, tacrolimus, sirolimus, and mycophenolate mofetil, the cost of surveillance biopsies at 6 and 12 months, and all standard lab testing and procedures performed following kidney transplantation. There will be no charge to the subject for additional blood testing that may be done as part of this protocol or the 24-month biopsy since it is not a part of standard care at this center.

**b. Will financial obligations of the subject be increased as a result of procedures performed solely for research purposes?**

All standard of care treatment will be the responsibility of the participant. Kidney transplant recipients require periodic visits and blood testing as part of standard treatment. Participants in this study may have more frequent visits because of their enrollment in the study. A kidney biopsy at 24 months is not considered standard care at this institution. Funding has been sought to cover the cost of the research-related procedure and the subject/subject’s third party payer will not be charged.

**21.** **Financial Compensation to the Subject for Participation**

**Will the subject receive any financial compensation for participation?**

Subjects will not receive any financial compensation for participation.

**POTENTIAL CONFLICTS AND PRIOR REVIEW (22-23)**

**22.** **Potential Financial Conflict of Interest**

**Does any investigator, participating physician or health care personnel (or any immediate family member [spouse, child, or sibling] of above) have a potential financial conflict of interest as defined by UNMC or University of Nebraska Board of Regents policy?**

No known potential financial conflicts of interest exists with the investigators, secondary investigators, participating physicians, health care personnel, data and administrative personnel, and/or any family members of the previously mentioned individuals.

**23. Prior IRB Review**

**a. Has this study (or one substantially similar) been previously submitted to the UNMC IRB and then withdrawn by the investigator for any other reason?** No, this study or one substantially similar has not been previously submitted to the UNMC IRB and then either withdrawn by the investigator or denied approval by the board.

**b. To the best of your knowledge, has this study (or one substantially similar) been considered by another IRB and not granted approval?**

To our knowledge, neither this study nor one similar has been considered and/or denied approval by another IRB.

